## Background

1.

Congestive heart failure (CHF) causes significant morbidity and mortality. At least 50% of patients have one or more comorbid conditions such as type II diabetes, coronary heart disease, chronic kidney disease, hypertension, and others. Patients diagnosed with CHF take multiple medications and prescribed complex treatment regimens. Good health literacy is needed to action diet, complex self-management skills, and maintain compliance life-long (1, 2). In addition, interacting effectively with health systems is required for lifestyle maintenance, behavioural changes, and consolidation of chronic disease self-management (CDSM). Patients and health system factors can act as barriers to optimal care, including developing new comorbidities, geography (isolation and remoteness), language, culture, education and socio-economic disadvantage, social supports, and negative attitudes towards establishments (3). Hospital readmissions are high, with 25–50% occurring within 1–6 months of discharge; this largest cost contributor is also preventable and amenable, as studies have demonstrated the care process (4). Better healthcare delivery systems could be achieved by the addition of patient self-management capabilities within programmes that meet patient needs and link health services (4, 5).

Chronic disease management and CHF programmes share similar care domains, one aspect is CDSM. Despite setbacks, there is optimism that CDSM will provide increasing importance to CHF programmes. Nevertheless, to an increasing extent, translational issues such as the containment of resource utilisation and cost blowouts must be factored into the aims of CDSM. These are, however, not the primary aims of large randomised controlled trials. These translational issues are better understood when exploring a patient’s journey. When patients seek health services, the acuity determines if interactions are in the community or *via* acute services such as ambulance, emergency, and hospital admissions. Following acute care, patients then transition back to the community. This process creates new information, new members of a health team, and may also create silos. There are CHF patients that inadvertently utilise the acute pathways and are potentially preventable admissions. It is thus vital that CDSM research aligns with clinical and administrative realities.

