## Patient cohort and selection criteria

4.

A minimum of 40 patients with CHF who meet the inclusion criteria will be offered an opportunity to participate. In uncertain cases, subjects will be considered eligible if the review of medical records demonstrates that they have a CHF diagnosis based on ACC/AHA and National Health Data Dictionary standardised definitions (1, 2). The project physicians will perform this. An independent physician will review uncertain cases.

Eligible patients will be: aged over 18 years; able and willing to provide informed consent; started SGLT-2i within 6 months - for systolic HF (echocardiographic EF <40%); receive one aspect of CHF care within a defined study health corridor.Patients will be excluded: If concerns are raised by any medical staff, the patient has a life expectancy of ≤6 months whilst receiving palliative or nursing home care. Cognitive status and dementia will not be a contraindication if there is consent from a caring relative or legal guardian and the ability to complete the CFPI; have a significant neurological/cognitive impairment or are unable for any reason to provide written informed consent; do not usually reside within the region (or for whom no follow-up data can be obtained); started SGLT2-i for more the >6 months.*Health Staff* will be sent surveys if they manage chronic diseases, including CHF and are willing to complete an Assessment of Chronic Illness Care (ACIC) questionnaire.

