### Study timelines and follow-up project milestone

5.14.

Study recruitment will commence in September 2021 and end in September 2022 (12 months). A census of all outcome data will be conducted in December 2022. There should be >40 potentially eligible patients over the 12-month recruitment and follow-up period.

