### Statistical aspects and data analysis

5.15.

The study cohort assesses feasibility, which will allow appropriate parameters to determine sample size power calculations for future studies that will utilise a controlled design. Initial data analysis will investigate the distribution characteristics of each primary and secondary outcome measure and determine either a parametric or semi-parametric statistical approach to main data analysis. A combination of descriptive statistics, linear mixed models, and generalised estimating equations will be used to calculate and present data. If continuous outcome data are approximately normally distributed, then linear mixed models (LMMs) will be used to examine change over time for each measure at intra-and inter-individual levels. If the distribution of outcome data is more amenable to a semi-parametric approach, then we will use generalised estimating equations (GEEs) to calculate an average estimate of the intervention effect for the cohort. Descriptive statistics for baseline demographics and clinical characteristics will be presented as means (standard deviation) for continuous data and count (percent) for categorical data. As an example, the previous publication provides estimates for pilot sample size calculations for categorical data. A future RCT of 200 patients in each arm for effects size of 25% reduction in readmission at 12 months established an event rate of 1,600 readmissions at 12 months (25–50% historical rate at 1 and 6 months), 90% power, and 5% two-sided significance, and 25–75 patients are published recommendations for small to large, standardised effect sizes (30). With the introduction of SGLT-2, the population level effect size is not known, and we have chosen >40 patients with an LVEF <40% and a NYHA class of 2 or 3. The event rates are well documented as 25% for 1-month readmission and 1-year mortality. Follow-up at 12 months predicts >100 admissions and > 10 mortalities. Interim analysis will ensure that this modelling supports the study goals.

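### The projection of more than 100 admissions in about 40 patients is roughly 1.8 to 2.5 times what the plan's own 1-month and 6-month readmission rates support

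*Protocol article*

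**What the plan says.** All the planning figures are in section 5.15 (Statistical aspects and data analysis). The cohort is described as follows: "we have chosen >40 patients with an LVEF <40% and a NYHA class of 2 or 3". The rates come next: "The event rates are well documented as 25% for 1-month readmission and 1-year mortality". The projection follows directly: "Follow-up at 12 months predicts >100 admissions and > 10 mortalities". An interim analysis is then to check that this modelling supports the study goals.

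Earlier in the same paragraph, a future randomised trial of 200 patients per arm is said to have "established an event rate of 1,600 readmissions at 12 months (25–50% historical rate at 1 and 6 months"). The Background gives the same range and makes clear that the clock starts at discharge: "Hospital readmissions are high, with 25–50% occurring within 1–6 months of discharge".

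What the 40 counts is not fixed. The Abstract speaks of recruiting more than 40. Section 4 says: "A minimum of 40 patients with CHF who meet the inclusion criteria will be offered an opportunity to participate". Section 5.14 says: "There should be >40 potentially eligible patients over the 12-month recruitment and follow-up period". NYHA class 2 or 3 appears in section 5.15 but is not among the eligibility criteria in section 4.

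Section 6 (Discussion) names the anticipated event rates as a strength that lets this sample size inform a later randomised study.

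**The concern.** More than 100 admissions in 40 patients means at least 2.5 per patient per year. A population in which half are readmitted by 6 months would not be expected to reach that, and the article does not show how the figure was obtained. The percentages also describe patients just discharged from hospital. This study recruits at community cardiology outpatients and support services (section 5.5), and section 4 requires no index admission.

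The number is relied on in two places: section 6 uses the anticipated event rates as an argument for the study's value to a later trial, and section 5.15 makes the modelling the benchmark for the interim analysis. Readmission is also among the primary outcomes (section 5.12). An inflated yield makes the study look better able to estimate a readmission rate, and to assess prediction of readmission, than it will be. Repeat admissions in one patient are not independent, so even the correct count overstates the information available.

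**Working it through.** **Inputs, all from section 5.15 unless noted**
- N = 40, the floor of the stated size, each followed for 12 months (section 5.5).
- 25% readmitted at 1 month; 25% dead at 1 year.
- "25–50% historical rate at 1 and 6 months", read as cumulative proportions of 25% by month 1 and 50% by month 6.
- Future trial: 2 x 200 = 400 patients and 1,600 readmissions in 12 months.

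**Step 1. Reproduce the plan's figures**
- Deaths: 40 x 0.25 = 10, so more than 40 patients gives more than 10. This agrees.
- Admissions, with 25% applied in every month: 40 x 0.25 x 12 = 120.
- Allowing for follow-up lost to death: the yearly death hazard is -ln(0.75) = 0.288, so the mean fraction of the year lived is 0.25/0.288 = 0.869, and 120 x 0.869 = about 104.

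Both exceed 100, so a flat 25% per month reproduces the projection.

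**Step 2. Test that assumption against the plan's 6-month figure**
- A flat 25% per month gives 1 - 0.75^6 = 1 - 0.178 = 82% readmitted by 6 months.
- The plan says 50%. The first-month rate cannot hold through the year if the 6-month figure is right.

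**Step 3. Recompute so that 50% at 6 months is respected**

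| Assumption | Calculation for 40 patients | Admissions in 12 months |
|---|---|---|
| 50% in each half-year | 40 x 0.5 x 2 | 40 |
| 25% by month 1, 50% by month 6, later hazard continued | monthly hazard after month 1 = (0.693 - 0.288)/5 = 0.0811; 40 x (0.288 + 11 x 0.0811) = 40 x 1.18 | 47 |
| Constant hazard giving 50% at 6 months | 40 x 12 x 0.693/6 = 40 x 1.386 | 55 |
| Same two-step pattern, restarting after every admission (simulated) | 40 x 1.40 | 56 |

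The range is 40 to 56, or 1.0 to 1.4 per patient-year. Against 100, the ratios are 100/56 = 1.8 and 100/40 = 2.5. Conversely, 100 admissions would need about 100/1.40 = 71 to 100/1.0 = 100 patients. The table ignores deaths. The 0.869 factor would lower the two constant-rate rows from 40 to about 35 and from 55 to about 48.

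**Step 4. The 1,600 figure**
- 1,600/400 = 4.0 per patient-year, against 1.0 to 1.4 from 50% at 6 months.
- It is above even a flat 25% per month: 400 x 0.25 x 12 = 1,200.
- Scaled to this cohort, 40 x 4.0 = 160.

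One paragraph therefore carries three rates that cannot all hold: 1.0 to 1.4, 3.0 and 4.0 admissions per patient-year.

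**The case against.** The best defence is that the sentence just before the projection gives 25% at 1 month, and carrying this through the year yields 120, or 104 after mortality. One of the plan's own rates therefore supports the figure, and the fault is inconsistency between inputs, not a failed sum. This stands as an account of where the number probably came from. It does not rescue the number, because the step is unstated and contradicts the 50% given for 6 months in the same paragraph.

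It can also be said that this is a hypothesis-generating feasibility cohort with an interim check already planned. That limits the consequences. It does not supply a sound benchmark for the check.

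Some stronger readings are tempting and are not supported:
- **That the 1,600 contradicts the projection.** It scales to 160 in 40 patients, and the projection is a lower bound, so the two are compatible. The 1,600 conflicts with the 6-month rate, and it errs towards more admissions. It is also attributed to an earlier publication that is not at hand, so nothing can be said about how it arose.
- **That the sample size has lost its justification.** Section 5.15 does not derive N from the admission count. It cites published recommendations of 25 to 75 patients and says the effect size is unknown. More than 40 remains inside that range.
- **That the excess is about fourfold.** This needs 25% at 6 months, which gives about 23 admissions (40 x 12 x 0.288/6). The plan already has 25% readmitted by month 1.
- **That the deaths projection is wrong too.** It reproduces.

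**Conclusion.** The point holds for the admission projection. With the rates read as 25% at 1 month and 50% at 6 months, 40 patients followed for a full year give about 40 to 56 admissions, so the projection is about 1.8 to 2.5 times too high. The result rests on that reading of the range, on the percentages being cumulative proportions of patients, on N = 40, and on no loss of follow-up to death. The overstatement may be greater in practice, because rates counted from discharge are applied to outpatients who need not have been admitted. The documents give no rate for such patients, so that part cannot be quantified.

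What fails is the event-yield projection, as a strength in section 6 and as the interim benchmark. The unsettled meaning of 40 and the NYHA wording are secondary. They matter because any event count scales with the patients actually enrolled and depends on who they are.

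**What to change.** Rewrite the closing part of section 5.15:
1. Restate the projection as about 40 to 56 admissions per 40 enrolled patients over 12 months, showing the per-patient-year rate (1.0 to 1.4), its source and the assumptions. Add that the source rates run from discharge and may be too high for this cohort. Keep the deaths figure.
2. Reconcile the 1,600 readmissions with 50% at 6 months, or stop using it as a planning input.
3. State that 40 means patients enrolled, and use the same term in the Abstract and in sections 4, 5.14 and 5.15.
4. Make the NYHA class 2 or 3 wording in section 5.15 agree with the eligibility criteria in section 4.
5. Base planning of the randomised trial on the observed admissions per person-time, with a confidence interval that allows for repeat admissions within patients (for example, a robust or negative binomial variance).
6. Adjust the strength claimed in section 6 and the interim benchmark to the restated figure.

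The cost is a rewritten paragraph, small wording changes elsewhere and a less favourable stated event yield. No extra patients are needed.

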### Patient and public involvement

5.16.

The development of this study was informed by the high rate of heart failure readmissions and poor uptake of CDSM programmes. No patients were involved with the study design; however, both experience and the published literature supported these directions. Patients will be provided feedback upon study completion. Public involvement has occurred during the formulation of the study and generic tools such as the CFPI. Further efforts will be made to provide community engagement, especially *via* focus groups.

### Ethics and dissemination

5.17.

This study has been approved by St Vincent’s ethics committee (approval no. LRR 177/21). All participants will complete a written informed consent prior to enrolment in the study. The study results will be disseminated widely *via* local and international health conferences and peer-reviewed publications.

## Discussion

6.

Congestive heart failure programmes utilising CDSM raise broad questions about the paradigms for evidence, followed by clinical translations for health services research. In contrast, pharmacological and device-based therapies have achieved class 1 and Level A evidence; similarly, physical exercise and organised programmes including cardiac rehabilitation have secured evidence in clinical guidelines (1, 2, 5, 12, 27, 28). CDSM is a complex intervention that aims to achieve better contextual self-management efficacy for an individual’s chronic ailment. CHF clinical trials using therapeutics predominately explored *major adverse cardiovascular events* (MACEs) as primary endpoints, and with clinical pathophysiological changes, cost, quality, and disability of life, as secondary endpoints. Diagnostic tools and instruments to test CHF and life measures are also established (13–17, 29). The established evidence base is consolidated into organised frameworks such as guidelines (1, 2, 12), taxonomies (5), and processes of care (12–17) (Figure 1). The study approach we undertake for CDSM in HF utilises a mixed-methods approach, whereas, with qualitative research, it is harder to achieve higher levels of evidence. In this study, the first phase is an evidence review to standardise the trial protocol on current published guidelines; the second phase balances the qualitative and quantitative arms to reflect the true nature of the processes in question. For example, in the 2020 guideline revision of CHF clinical measures, patient self-care education was changed from a performance measure to a quality measure, citing concerns about the limitations in the evidence for improved outcomes (22–25). It is thus time to ponder on how to best rebuild the evidence. In addressing the specific challenges for this study and also in creating hypotheses for future studies, we highlight the following strengths and limitations:

A strength of this study is the ability of the observational sample size to inform a future randomised study, by the event rates anticipated with the CHF inclusion criteria (LVEF <40%). In Australia, an SGLT-2i can be provided to all patients with NYHA class II and LVEF <40%; thus, its use requires a standardised baseline, and it requires education on self-management to use it safely. In addition, we were also able to leverage on previous works which established performance measures (5, 12, 13, 15, 16, 29) some updated (14), to inform and extract parameters for this study.

An important limitation in study-specific tools is questionnaires that have qualitative and quantitative components [Tables 2, 3 previously published (3)]. The frameworks for CDSM and CPFI (11) have been previously detailed. These goals (11, 19–21) and established CHF readmission risk scores were foundations on which the SCRinHF tool was modelled. The limitations of traditional tools, including patient fatigue (45–60 min to complete), were the impetus for the development of a one-page tool; overlaps in questions between tools and investigators were the motivation to train end users to populate other tools with overlapping questions where appropriate [previously published Table 2 Iyngkaran et al. (3)]. Monitoring clinical changes with CHF is also important. The balance between quick and less accurate assessments such as NYHA classification, general chronic disease scores, and CHF-specific scores can impact clinical standardisation and require thoughtful considerations (30–34). These points will also be factored in when informing a larger definitive RCT.

*Generic limitations and strengths*: The study design is hypothesis generating, and results may reflect a degree of subjectivity. Generalisability of results will not be answered in this study. Standardising training of study case workers that arise from different allied health backgrounds, that bring a different perspective to health provision will be difficult. There was no background data to draw from in determining sample size and ensuring the validity and reliability of the qualitative tools including PACIC and PIH scales. The level of engagement with the wider communities has also been limited at this stage. This will however be addressed when there are clear working hypotheses, with an improved understanding in this area, that could contribute to the design of a larger more focused study, involving community participation. The Delphi method will be published when the data are available from Phase 2.

In conclusion, the specific challenges highlighted will be addressed in the creation of hypotheses for future studies. Areas that will be challenging include the CDSM programme for clients from diverse/lower educational and socioeconomic backgrounds where the programme may have variable effectiveness. Delivery to clients placed at the apex of the health pyramid and engagement in primary care has shown the greatest health impact (8, 9, 21). With scoring, patient perceptions of illness are qualitative and hard to standardise. Scales such as The European Heart Failure Self-care Behaviour Scale (EHFScBS) and Self-care Heart Failure Index (SCHFI), amongst 14 other HF self-care instruments, have proven reliability and validity; however, they do not adequately address co-morbidities (8, 9, 21). Demographic heterogeneity is also greater outside Phase 3 trials. The themes that emerge at the population level include cultural sensitivity, patient-centred care, creating specific policies for disparity, emphasis on accuracy and detail of information, engaging extended families, and providing tools to facilitate health provider–patient relationships within the larger socio-cultural system (5). All these factors will be relevant as this study evolves.

## Strengths and limitations

Explores a simple user-friendly self-management and readmission tool.Self-management programmes can be complex with few gold standard publications.Enrols a diverse cohort of congestive heart failure patients.Elements are hypothesis-generating, e.g., a scoring system for the *SCRinHF* tool has not been tested.Improves our understanding of self-management scores in heart failure but will require a larger study to corroborate findings.

